### Intervention

Peer2Me is a 1:1 mentoring program that aims to support acutely ill young adults with cancer with the help of a mentor in their immediate coping with the disease, thereby increasing their experience of self-efficacy and reducing their psychological distress. Between 2019 and 2020, a pilot study was conducted to evaluate the feasibility and utilization of this mentoring project [50].

The mentor’s support is intended to meet the need for emotional or psychosocial support. She or he assumes the role of a communication partner using her or his experience to help the mentee cope with the disease and the course of treatment.

Once mentors have been recruited, and if the results of the SCID and the initial interview are successful, they will attend mentor training. Participation in this training, which includes self-awareness components, is mandatory for mentors. The two-day training (6 h per day) takes place in a face-to-face or online setting in Hamburg or Leipzig with 10 to 12 participants and is conducted by psycho-oncologically experienced study staff. The content of the training includes basic client-centered communication skills and elements of motivational interviewing [51, 52]. This is intended to introduce the mentors to appropriate interview techniques such as active listening, open-ended questions, etc. In addition, the mentors are given the opportunity to learn about and reflect upon their role as a “former patient” and as a mentor. In this context, the boundaries of the mentors play an essential role. It is important that the mentors are protected in their role, are not pressured to act as medical experts or psychotherapists and are not expected to be able to answer expert questions. They should also be able to distance themselves from potentially excessive or inappropriate expectations of mentees. Other components include the acquisition of skills and exercises to improve disease management. In addition, mentors are provided with general medical (common tumor entities, long-term sequelae) and basic psychosocial knowledge about cancer in young adulthood and existing support services for the AYA patient group, such as support groups or cancer counseling centers. Both mentors and mentees also receive a folder with information (brochures, flyers, guides), and the latter will be able to contact their mentor, if they have any questions.

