The intervention begins by matching the tandems (mentor and mentee) by age, diagnosis, and gender, if possible. At the first meeting of each tandem, a study staff member will be present to explain the Peer2Me study process and agenda, distribute cancer-specific and psychosocial information materials, and to conduct the baseline assessment (t1). Participants are either provided with a link to complete the standardized study questionnaire online using Lime Survey, or, if preferred, a printed version of the questionnaire is sent.

The tandem itself will then determine the frequency, duration, and type (face-to-face or telephone) of subsequent contacts between mentor and mentee over the following three months. However, at minimum of 4 documented contacts should take place for the purposes of the evaluation (fewer than 4 contacts are considered as a termination of intervention). The mentor documents each interaction, including the key issues discussed with the mentee, and informs the study team. After 3 months, a formal final meeting of the tandem will be held together with a member of the study team, during which the assessment t2 is conducted. The final survey (t3) will be sent to all mentees 3 months after the intervention.

Group supervision for the mentors will take place once a month. It will be provided by a psychologist with appropriate psycho-oncological and group therapy expertise.

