### Statistical analysis

#### Power and sample calculation

The number of cases was planned with the GPower program using a significance level of α = 0.05 and a power of (1-ß) = 0.8070. The primary outcome measure self-efficacy is used to demonstrate the effectiveness of the intervention. We make the following assumptions about changes in the intervention and control group: The pre-post effect size used is the effect size for self-efficacy.

d = 0.43, which could be found in the literature [68]. The expected controlled effect size requires a minimum of 90 subjects per group (180 subjects in total) measured with the U-test for independent groups. For this group size (*N* = 180), an analysis of variance with repeated measures (two groups, three measurements, correlation between measurements *r* = 0.5, epsilon = 1) can already demonstrate the following small effects: for comparisons between factors (IG vs. CG): f > 0.17; comparisons within factors (across measurement time points): f > 0. 09; and interaction effects between the two groups and time: f > 0.09. The sample thus has sufficient power to detect at least medium effects between the groups, as well as small effects within the groups and small interaction effects between the groups considering the measurement time points.

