#### Statistical methods

Quantitative data will be analyzed using the statistical program SPSS 29.0 [69]. First, the items of the scales of the primary and secondary outcomes are checked for missing values. Items and complete sociodemographic variables that violate the MCAR (missing completely at random) assumption are identified in each subanalysis using Little’s MCARTest. Missing values are then estimated using the Markov Chain Monte Carlo (MCMC) procedure. This procedure yields reliable results even with high proportions of missing values for both the MCAR and MAR (missing at random) missing value patterns. On the other hand, it is suitable for any patterns of missing values, but also for monotonic patterns.

Descriptive analyses are calculated for all variables and presented as frequencies, means, standard deviations and ranges. Sociodemographic and medical predictors of intervention effectiveness are identified using stepwise backward regression. Non-dichotomous categorical characteristics are first subjected to multifactorial analysis of variance. Games-Howell correction or Bonferroni-Holm correction is used as a post hoc test, as appropriate. Correlation analysis is performed prior to each regression to avoid multicollinearity. Mean comparisons using one-way factor repeated measures analyses of covariance (ANCOVA) are used to test the hypotheses.

The first step is to compare only the randomized groups. In the next step, the preference groups are analyzed to determine differences in the effects compared to the randomization groups. Finally, all four groups are compared with each other, adding an indicator variable (randomization/preference) as a covariate. If the number of randomized study participants is too small, the data must be analyzed as a prospective cohort study.

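### The planned test and sample size make no allowance for mentees who share a mentor; if any mentor is reused, the standard error is somewhat too small

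*Protocol article*

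**What the plan says.** **Analysis.** Statistical methods gives the test: "Mean comparisons using one-way factor repeated measures analyses of covariance (ANCOVA) are used to test the hypotheses". The only covariate named for the group comparison is the indicator for randomised versus preference participation, which enters when all four groups are compared. No mentor factor or random effect is mentioned.

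**Sample size.** Power and sample calculation takes an effect size of "d = 0.43, which could be found in the literature [68]" and concludes: "The expected controlled effect size requires a minimum of 90 subjects per group (180 subjects in total) measured with the U-test for independent groups". The supporting repeated-measures calculation assumes "two groups, three measurements, correlation between measurements *r* = 0.5, epsilon = 1". The only correlation allowed for is therefore within a person over time.

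**Delivery.** Under Intervention, Peer2Me is a 1:1 mentoring programme lasting three months: "The intervention begins by matching the tandems (mentor and mentee) by age, diagnosis, and gender, if possible". Each tandem sets the frequency, duration and type of its own contacts. Mentors are trained in two-day courses "with 10 to 12 participants". Under Control group, controls have one standardised 30-minute consultation and no mentor.

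**Silence.** The article does not give the number of mentors, and it does not say whether a mentor may accompany a second mentee after, or alongside, the first.

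**The concern.** The mentor is the active ingredient of the intervention, and mentors will differ in skill, availability and style. Two mentees of the same mentor share that mentor's effect, so their outcomes are likely to be positively correlated. A repeated-measures ANCOVA with no mentor term, like a U-test, takes all patients within an arm as independent.

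If mentors are reused, the variance of the intervention-arm mean is larger than the analysis assumes, while the control arm is unaffected. The p-value for Peer2Me would then be too small, and a test with the correct standard error would have less than the stated power. The sample size has no reserve to absorb this, because 90 per arm only just reaches 80%.

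Reuse is possible on the article's own figures. Recruitment runs from January 2021 to June 2024, about 42 months, against a three-month intervention. One mentor per mentee would need 90 trained mentors for the randomised arm alone, which is 90/12 = 7.5 (so 8) to 90/10 = 9 courses. Patients who choose Peer2Me by preference would need more. If randomised and preference mentees draw on the same mentors, the four-group comparison is exposed as well.

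**Working it through.** **Inputs from the article.** Effect size d = 0.43; n = 90 per arm; U-test; α = 0.05, taken as two-sided because that reproduces the sample size; power taken as 0.80. The article prints "a power of (1-ß) = 0.8070", probably 0.80 run together with a reference number. Using 0.807 would give 92 per arm.

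**Inputs assumed, not in the article.** Mentees per mentor, m, equal for all mentors: 1 to 5. Mentor intraclass correlation, ρ: 0.05 to 0.10. Total variance is held equal in both arms.

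**Step 1: reproduce the plan's figure.** The U-test has relative efficiency 3/π to the t-test under normality, so 90 per arm acts like 90 × 3/π = 85.9. Noncentral-t power at d = 0.43 is then 0.8003, and 90 is the smallest number per arm that reaches 0.80. The stated 90 is reproduced with no design effect in it.

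**Step 2: partially nested variance.** The design effect applies in the intervention arm only:

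- DE = 1 + (m − 1)ρ
- naive variance of the difference = 2σ²/n
- true variance = (1 + DE)σ²/n
- SE ratio (true/naive) = √[(1 + DE)/2]
- actual α = 2[1 − Φ(1.96/SE ratio)]
- power of a test with the correct SE = Φ(0.43/√[(1 + DE)/85.9] − 1.96)
- n per arm for 80% power = (1 + DE)(1.960 + 0.842)²/(0.43² × 3/π)

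Example, m = 3 and ρ = 0.10: DE = 1.20; SE ratio = √1.10 = 1.049; α = 2[1 − Φ(1.869)] = 0.062; SE = √(2.20/85.9) = 0.160; power = Φ(2.69 − 1.96) = 0.767.

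| m | ρ | DE | SE ratio | actual α | power at 90/arm | n/arm for 80% |
|---|---|---|---|---|---|---|
| 1 | any | 1.00 | 1.000 | 0.050 | 0.805 | 89 |
| 2 | 0.05 | 1.05 | 1.012 | 0.053 | 0.795 | 92 |
| 2 | 0.10 | 1.10 | 1.025 | 0.056 | 0.786 | 94 |
| 3 | 0.05 | 1.10 | 1.025 | 0.056 | 0.786 | 94 |
| 3 | 0.10 | 1.20 | 1.049 | 0.062 | 0.767 | 98 |
| 5 | 0.05 | 1.20 | 1.049 | 0.062 | 0.767 | 98 |
| 5 | 0.10 | 1.40 | 1.095 | 0.074 | 0.730 | 107 |

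The table uses the normal approximation, so its no-clustering row reads 0.805 and 89 rather than the 0.8003 and 90 of Step 1. Differences between rows should be read against that first row.

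**Step 3: variance scale.** For m = 2, ρ = 0.05 to m = 3, ρ = 0.10, the true variance is 2.5% to 10% above the naive one. The naive variance is thus understated by 1 − 1/1.025 = 2.4% to 1 − 1/1.10 = 9.1%.

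**Step 4: simulation under no treatment effect** (90 per arm; 20,000 trials for the t-test, 5,000 for the U-test). Rejection rates for t and U were 0.051 and 0.049 (m = 2, ρ = 0.05), 0.062 and 0.061 (m = 3, ρ = 0.10), and 0.074 and 0.075 (m = 5, ρ = 0.10). This agrees with the formula.

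These figures are for a two-group comparison at one time point, which is the scale of the plan's own sample-size calculation. In the ANCOVA, ρ would be the correlation left after the covariates.

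**The case against.** The strongest objection is that the decisive fact is absent: nowhere does the article say that two mentees share a mentor. The programme is described as 1:1. Secondary outcomes and Table 1 schedule the mentors' own measures once at t1 and once at t2, around one three-month intervention, which is what one would write if each mentor had a single tandem. Eight or nine courses over about 42 months at two centres is roughly one every five months, which is feasible, and matching on age, diagnosis and gender calls for a broad pool of mentors anyway. The article is also condensed, and a full protocol or analysis plan could hold a caseload rule or a mentor term.

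Most of this stands. A reader might infer that mentors are in fact reused and that the p-value will be wrong. The article does not support that: its text fits one tandem per mentor as well as it fits reuse, and the course arithmetic shows only that reuse is possible. A reader might also settle on a type I error near 8.6%. That needs every mentor to take four mentees and an intraclass correlation of 0.20 (DE = 1.60, variance ratio 1.30), and the article gives no basis for either value.

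What the objection does not remove is that the test and the sample size are stated, not left open. Both assume independent patients, and nothing in the text guarantees the condition under which that is correct. The description 1:1 defines the tandem; it does not cap a mentor's total number of mentees.

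**Conclusion.** The point holds conditionally. As published, the hypothesis test and the 90 per arm are right if each mentor has exactly one mentee, and mildly anti-conservative if some have more. At 2 to 3 mentees per mentor and an intraclass correlation of 0.05 to 0.10, two-sided α is about 5.3% to 6.2% and power at 90 per arm about 79.5% to 77%. Heavier reuse, at 5 per mentor and 0.10, gives about 7.4% and 73%. If only some mentors repeat, the effect is smaller than the table row for that m. Both m and the intraclass correlation are assumptions, so these figures show a range and do not estimate the trial's actual error. The matter is a cheap improvement to the stated analysis, not a demonstrated error in the result.

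**What to change.** 1. State whether a mentor may take more than one mentee, and that the 80% power assumes no mentor clustering.
2. Keep the mentor identifier of each tandem in the mentee data set, and report the distribution of mentees per mentor separately for the randomised and the preference groups.
3. Fix the rule in advance. If no mentor has more than one mentee, keep the planned analysis. If any does, test the hypotheses with a partially nested mixed model: a random mentor effect in the intervention arm only, each control as its own unit, residual variances by arm, and small-sample degrees of freedom. Mentor-clustered standard errors are an acceptable alternative. In the four-group comparison, a mentor who serves both randomised and preference mentees should carry the same identifier.

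**Cost.** One variable and a few sentences. Mentors already document their contacts and report them to the study team, so the link should be recoverable, although the article does not say that an identifier is stored. If mentors repeat, the interval will be slightly wider. If only a few repeat, the mentor variance will be imprecise and may be estimated at zero, which should be reported as such.

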## Discussion

Young adults with cancer are exposed to disease- and treatment-related stressors as well as various psychosocial stressors [27, 70]. Existing psycho-oncological research shows that AYA have unmet needs for information and support [71, 72]. Social support is crucial for this patient group, and in addition to family and friends, social interactions with peers play an important role [73, 74]. While social support from friends is very important for cancer patients of all ages, young adults with cancer may find it particularly difficult to share experiences and concerns with peers who are not affected by the illness in this age group. To date, there are only few evaluated peer-supported interventions in a one-to-one and face-to-face setting available to date that address the needs of young adults with cancer, either internationally and nationally [50, 75]. For this reason, the intervention was developed to promote interactions between young adult cancer patients that are beneficial to both groups of participants (mentors and mentees). Particularly in the acute phase of the illness, AYAs seek personal 1:1 contact with a young adult cancer survivor. Due to the shared experience in dealing with cancer and its effects and the non-hierarchical and reciprocal relationship between the participants, mentoring is an effective form of emotional and social support. At the end of the study, based on a proof of efficacy, an appropriate psycho-oncological intervention for young adult cancer patients undergoing acute treatment will have been developed. The long-term continuity of the program is planned to be ensured through collaboration with different partners.

## Data Availability

The datasets generated and analyzed during the current study are not publicly available due to required data protection regulations in patient information (which assures participants that the data are not passed on to third parties) but are available from the corresponding author upon reasonable request.
